## Abstract

**Background:**

Early identification of a patient with infection who may develop sepsis is of utmost importance. Unfortunately, this remains elusive because no single clinical measure or test can reflect complex pathophysiological changes in patients with sepsis. However, multiple clinical and laboratory parameters indicate impending sepsis and organ dysfunction. Screening tools using these parameters can help identify the condition, such as SIRS, quick SOFA (qSOFA), National Early Warning Score (NEWS), or Modified Early Warning Score (MEWS). We aim to externally validate qSOFA, SIRS, and NEWS/NEWS2/MEWS for in-hospital mortality among adult patients with suspected infection who presenting to the emergency department.

**Methods and analysis:**

PASSEM study is an international prospective external validation cohort study. For 9 months, each participating center will recruit consecutive adult patients who visited the emergency departments with suspected infection and are planned for hospitalization. We will collect patients’ demographics, vital signs measured in the triage, initial white blood cell count, and variables required to calculate Charlson Comorbidities Index; and follow patients for 90 days since their inclusion in the study. The primary outcome will be 30-days in-hospital mortality. The secondary outcome will be intensive care unit (ICU) admission, prolonged stay in the ICU (i.e., ≥72 hours), and 30- as well as 90-days all-cause mortality. The study started in December 2021 and planned to enroll 2851 patients to reach 200 in-hospital death. The sample size is adaptive and will be adjusted based on prespecified consecutive interim analyses.

**Discussion:**

PASSEM study will be the first international multicenter prospective cohort study that designated to externally validate qSOFA score, SIRS criteria, and EWSs for in-hospital mortality among adult patients with suspected infection presenting to the ED in the Middle East region.

**Study registration:**

The study is registered at ClinicalTrials.gov (NCT05172479).

## Introduction

Over the past decade, there has been continued focus on sepsis as a prevalent condition that accounts for 10% of admissions to intensive care units (ICUs) and is associated with a 10–20% in-hospital mortality rate [1–5]. Standardized protocols and physician awareness have significantly improved survival, but mortality rates remain high between 20% and 36%, with ~270,000 deaths annually in the United States [6–8]. It has been estimated that 80% of sepsis cases are identified and treated in the emergency department (ED), and the remainder develop sepsis during hospitalization with other conditions [7].

In 2016, the Society of Critical Care Medicine/European Society of Intensive Care Medicine (SCCM/ESICM) task force redefined sepsis based on organ dysfunction and mortality prediction [9–11]. Sepsis now is defined as life-threatening organ dysfunction caused by dysregulated host response to infection. This definition emphasizes the complexity of the disease that cannot be explained by infection or body response alone. Acute change in Sequential Organ Failure Assessment (SOFA) score ≥2 indicates sepsis-related organ dysfunction and is associated with in-hospital mortality. Systemic Inflammatory Response Syndrome (SIRS) and “severe sepsis” terms were omitted from the most recent definition. SIRS has been criticized for its poor specificity, while “severe sepsis” may underestimate sepsis’s seriousness. A subset of patients may develop septic shock with underlying profound organ dysfunction and excess mortality. Clinically, septic shock is defined as persistent hypotension requiring vasopressors to maintain mean arterial pressure (MAP) ≥ 65 mm Hg and serum lactate level ≥ 2 mmol/L (18 mg/dL) despite adequate volume resuscitation.

Early identification of a patient with infection who may develop sepsis is of utmost importance [12]. Unfortunately, this remains elusive because no single clinical measure or test can reflect the complex pathophysiological changes in patients with sepsis. However, multiple clinical and laboratory parameters indicate impending sepsis and organ dysfunction. Screening tools using these parameters can help identify the condition, such as SIRS, quick SOFA (qSOFA), National Early Warning Score (NEWS), or Modified Early Warning Score (MEWS) (Tables 1 and 2) [13].

**Table 1 pone.0281208.t001:** Component of qSOFA score and SIRS criteria.

Variable	qSOFA		SIRS	
	*Cut-off*	*Points*	*Cut-off*	*Points*
Altered mental status (GCS <15)	Yes	1	—	—
Heart rate (beats/min)	—	—	>90	1
Respiratory rate (breaths/min)	≥22	1	>20	1
Systolic blood pressure (mm Hg)	≤100	1	—	—
Temperature (°C)	—	—	<36 or >38	1
White blood cells count (x10^9^/μL)	—	—	<4 or >12 or >10% bands	1
	**Maximum score**	**3**	**Maximum score**	**4**
	**Positive cut-off value**	**≥2**	**Positive cut-off value**	**≥2**

***GCS*:** Glasgow Coma Scale; ***qSOFA*:** quick Sequential Organ Failure Assessment; ***SIRS*:** Systemic inflammatory response syndrome.

**Table 2 pone.0281208.t002:** Components of NEWS, NEWS2, and MEWS.

Variable	NEWS		NEWS2		MEWS	
	*Cut-off*	*Points*	*Cut-off*	*Points*	*Cut-off*	*Points*
AVPU	Alert	0	Alert	0	Alert	0
	VPU	3	CVPU*	3	React to voice (V)	1
	—	—	—	—	React to pain (P)	2
	—	—	—	—	Unresponsive (U)	3
HR (beats/min)	51–90	0	51–90	0	51–100	0
	91–110; or 41–50	1	91–110; or 41–50	1	41–50 or 101–110	1
	111–130	2	111–130	2	<40 or 111–129	2
	≤40 or ≥131	3	≤40 or ≥131	3	≥130	3
O_2_Sat (%)	≥96	0	≥96^†^	0	—	—
	94–95	1	94–95	1	—	—
	92–93	2	92–93	2	—	—
	≤91	3	≤91	3	—	—
Oxygen supp.	No	0	No	0	—	—
	Yes	2	Yes	2	—	—
RR (breaths/min)	12–20	0	12–20	0	9–14	0
	9–11	1	9–11	1	15–20	1
	21–24	2	21–24	2	<9 or 21–29	2
	≤8 or ≥25	3	≤8 or ≥25	3	≥30	3
SBP (mm Hg)	111–219	0	111–219	0	101–199	0
	101–110	1	101–110	1	81–100	1
	91–100	2	91–100	2	71–80 or ≥200	2
	≤90 or ≥220	3	≤90 or ≥220	3	≤70	3
Temperature (°C)	36.1–38	0	36.1–38	0	35–38.4	0
	35.1–36 or 38.1–39	1	35.1–36 or 38.1–39	1	<35 or ≥38.5	2
	≥39.1	2	≥39.1	2	—	—
	≤35	3	≤35	3	—	—
	**Maximum score**	20	**Maximum score**	20	**Maximum score**	14
	**Positive cut-off value**	≥5	**Positive cut-off value**	≥5	**Positive cut-off value**	≥5

***AVPU*:** Alert, verbal, pain, or unresponsive; ***HR*:** Heart rate; ***NEWS*:** National early warning score; ***NEWS2*:** National early warning score 2; ***MEWS*:** Modified early warning score; ***O***_***2***_***Sat*:** Oxygen saturation; ***RR*:** Respiratory rate; ***SBP*:** Systolic blood pressure.

*—Level of consciousness and new confusion (‘C’), thus AVPU becomes ACVPU, where C represents new confusion.

†—NEWS2 has a dedicated section (SpO_2_ Scale 2) for use in patients with hypercapnic respiratory failure who have clinically recommended oxygen saturation of 88–92%.

The 2016 SCCM/ESICM task force recommended using qSOFA [11], while the 2021 Surviving Sepsis Campaign strongly recommended against its use compared with SIRS, NEWS, or MEWS as a single screening tool for sepsis or septic shock [14].

Multiple studies have assessed qSOFA, SIRS, and EWSs validity in ED and showed conflicting results [15–21]. One systemic review compared qSOFA and EWSs (NEWS/Modified EWS [MEWS]) for predicting mortality and ICU admission when applied in the ED [13]. None of the eligible studies included NEWS2; and the authors of the review could not perform a meta-analysis due to marked heterogeneity in patient selection, definition of infection, outcomes, and settings. Moreover, studies have calculated the scores at different times. NEWS appeared more sensitive than qSOFA for predicting ICU admission and mortality at the commonly used thresholds (i.e., ≥2 for SIRS and qSOFA; ≥5 for NEWS, NEWS2, and MEWS), whereas qSOFA was more specific [13]. This correlates with previous criticisms of qSOFA, which have low sensitivity for early risk assessment [18–21].

We hypothesized that qSOFA has greater prognostic accuracy than SIRS and EWSs (NEWS/NEWS2/MEWS), and subsequently, aimed to reject the null hypothesis that all these predictive models have the same prognostic accuracy. Accordingly, we developed a protocol for a prognostic study to determine whether qSOFA has higher predictive performance for relevant clinical outcomes in adult patients with infection presenting to the ED. The primary outcome of this study is 30-days in-hospital mortality, and the secondary outcomes are ICU admission, prolonged ICU admission (i.e., ≥72 hours), 30- as well as 90-days all-cause mortality.

## Methods and analysis

### Study design and setting

This protocol describes a multicenter, prospective observational cohort study evaluating the prognostic accuracy of qSOFA score, SIRS criteria, and EWSs (NEWS/NEWS2/MEWS) for in-hospital mortality among adult patients presenting to the ED with suspected infection (NCT05172479). The study’s outlines are shown in Fig 1. The study duration is 12 months per center (9 months for recruitment and 3 months for follow-up). Recruiting centers and recruitment status are shown in Table 3 (July 2023).

### Diagnosis of infection

A presumptive diagnosis of infection will be judged based on the opinion of the ED physician upon the initial patient presentation. If required, two experts from each recruiting center will ascertain the diagnosis of infection on the 30^th^ day since inclusion to the study. Evidence of infection will be sought by analyzing the patient’s clinical, microbiological, and radiological data. Evidence of infection would be determined by either positive culture, other microbiological techniques (e.g., serological, or molecular), or radiological findings. If all of these evidence measures were equivocal, clinical context will be used to confirm the presence of infection. In cases of disagreement, consensus will be sought between the two experts. In all cases, the diagnosis of infection will be blinded to the output of the prediction models and the outcomes of patients.

### Study population

#### Inclusion criteria

PSSEM study will enroll all consecutive adult patients (age ≥18 years) presenting to the ED with suspected infection who are planned for hospitalization (Box 1).

Box 1. Eligibility criteriaInclusion criteria▶ Adult patient (ages ≥18 years).▶ Suspected infection (based on the opinion of the emergency physician).▶ Planned for hospitalization.Exclusion criteria▶ Presentation to ED is not due to infection (e.g., autoimmune diseases, myocardial infarction, stroke, venous thromboembolism, trauma, intoxication … etc.).▶ Pregnancy.▶ Transferred from another hospitals.▶ Code status is "Do-Not-Resuscitate" (DNR).▶ Elective admission to the hospital (i.e., not through emergency department).▶ Initial diagnosis of infection in the ED was not confirmed after finishing of the recruitment and follow-up phase.

#### Exclusion criteria

We will exclude patients who present to the ED due to non-infectious causes (e.g., autoimmune diseases, myocardial infarction, trauma, …etc.), pregnant woman, those who are transferred from other hospitals, or with “Do-Not-Resuscitate” (DNR) code status. Patients whose initial diagnosis of infection in the ED was not confirmed after the recruitment and follow-up will also be excluded (Box 1).

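### Enrolled patients are removed if infection is not later confirmed, so the analysed cohort is not the triage suspected-infection population that the study aims to validate in

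*Protocol article*

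**What the plan says.** The target population is suspected infection in most places where the Protocol article describes it.

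- The Abstract (Background) aims to "externally validate qSOFA, SIRS, and NEWS/NEWS2/MEWS for in-hospital mortality among adult patients with suspected infection".
- Study design and setting describes prognostic accuracy "for in-hospital mortality among adult patients presenting to the ED with suspected infection".
- Box 1 takes patients in on "Suspected infection (based on the opinion of the emergency physician").
- Table 4 defines infection for this study by the attending ED physician's opinion alone.
- Predictors and the Discussion fix the score inputs at the first triage measurement.

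The last exclusion then works on later information. The Exclusion criteria text says: "Patients whose initial diagnosis of infection in the ED was not confirmed after the recruitment and follow-up will also be excluded". Box 1 lists the same rule: "Initial diagnosis of infection in the ED was not confirmed after finishing of the recruitment and follow-up phase".

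Diagnosis of infection describes how confirmation is reached: "If required, two experts from each recruiting center will ascertain the diagnosis of infection", at day 30. They look at culture, other microbiology or radiology, and fall back on clinical context when these are equivocal. The section also states that "the diagnosis of infection will be blinded to the output of the prediction models and the outcomes of patients". The Discussion presents later confirmation as deliberate and pragmatic.

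**The concern.** A validation study should estimate how a score performs in the patients on whom it would be used. At triage the clinician knows only that infection is suspected. Whether the suspicion is later confirmed is unknown, so a confirmed-infection cohort cannot be picked out at the moment of scoring. Sensitivity, specificity, predictive values, AUC, calibration and mortality would then describe a different group from the one named in the aim.

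The removal may also be related to the outcome. The evidence that confirms infection accumulates with time and work-up. A patient who dies early may have less of it, and so may a mildly ill patient who is discharged quickly. Either route could change the mix of deaths and survivors, or of high and low scores, in the analysed set.

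**Working it through.** **1. When each piece of information arises**

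| Element | Where stated | When known |
|---|---|---|
| Suspected infection | Box 1, Table 4 | ED presentation |
| Score inputs | Predictors, Discussion | Triage (initial white cell count and pCO2 from the record) |
| Eligibility screening | Table 5 | Screening phase only |
| Primary outcome | Study outcome | Up to day 30 |
| Confirmation of infection | Diagnosis of infection | Day 30, if required |
| Exclusion if unconfirmed | Box 1, Exclusion criteria | After recruitment and follow-up |

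The last two rows come after the scores and at or after the close of the primary outcome window. The exclusion is therefore a post-baseline selection, although it is listed as an eligibility criterion.

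**2. The plan's own sample size** (Sample size section: 74 events in 879 patients, target of 200 events, 20% allowance)

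- Event rate: 74/879 = 8.42%.
- Patients for 200 events: 200/(74/879) = 2375.7.
- With the allowance: 2375.7 x 1.2 = 2850.8, rounded up to 2851. The stated figure is reproduced.
- Deaths expected after a 20% loss: 2851 x 0.8 x 74/879 = 192.0. The shortfall of 8 against 200 comes from multiplying by 1.2 instead of dividing by 0.8. It is separate from this point.

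**3. Deaths left after the exclusion**

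The share unconfirmed, u, is not given, so it is assumed here, with the same death rate in confirmed and unconfirmed patients. Deaths = 2851 x 0.8 x (1 - u) x 74/879, and the N that would allow for u on the plan's own method is 2850.8/(1 - u).

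| u (assumed) | Deaths expected | N to allow for u |
|---|---|---|
| 0% | 192 | 2851 |
| 5% | 182 | 3001 |
| 10% | 173 | 3168 |
| 20% | 154 | 3564 |

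The allowance in the Sample size section covers loss to follow-up and missing data. It does not mention unconfirmed patients.

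**4. Direction of the effect**

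Take 8.42% mortality in confirmed patients and u = 20%, and let unconfirmed patients have k times that mortality (k assumed). Mortality in all suspected patients is 8.42% x (0.8 + 0.2k).

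- k = 0.5: 7.6%
- k = 1: 8.4%
- k = 2: 10.1%

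The analysed cohort would show 8.4% in each case. It could overstate, match or understate mortality in the target population, and the documents do not say which.

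**The case against.** **The population is not described in only one way.** The last paragraph of the Introduction speaks of adults with infection, and the first exclusion in Box 1 removes presentations not due to infection. A confirmed-infection cohort fits that Introduction sentence. This stands as a reason to align the wording. It does not outweigh the aim, the design statement, the inclusion rule and Table 4, which all rest on suspicion, and the Box 1 item can be judged at presentation.

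**The rule is open and adjudication is blinded.** Both are true. A reader might infer that blinding cannot be kept when same-centre experts review clinical data at day 30. The documents do not support that as a finding: how the case files are prepared is detail that an article may leave to the full protocol. The point does not need it, since even perfectly blinded adjudicators see only the evidence that survival and work-up allowed.

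**Early deaths need not be dropped.** A reader might infer that patients who die before work-up is complete will be excluded. The clinical-context fallback means that they can still be confirmed. Dependence on survival is possible, not shown.

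**The loss of deaths can be repaired.** Interim re-evaluation at 25%, 50% and 75% of recruitment could restore the number of events. That stands, so the counts above apply before any such correction. It would not undo the selection.

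**The timing conflict is small.** In-hospital follow-up ends by day 30, so day 30 in Diagnosis of infection and the end of in-hospital follow-up in the Discussion largely coincide, apart from earlier discharges. The wording in Box 1 and Exclusion criteria may refer only to when the exclusion is applied. This needs tidying and is not a serious contradiction.

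**A statistical analysis plan could add analyses.** It could, but the exclusion is fixed here as an eligibility criterion, twice, and a later plan would inherit it.

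**Conclusion.** The point holds as a mismatch between the stated target population and the cohort to be analysed. It follows from the text alone and needs no assumption: enrolled patients are removed on information gathered after triage.

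Its numerical effect is not established. A reader might infer that the scores will look better, or worse, than they are. The documents support neither, because the share unconfirmed, the mortality of unconfirmed patients and the performance of the scores in them are all absent. Nor do they show that the ranking of the scores would change. The one figure that can be tied to the plan is the expected number of deaths: 192 on its own inputs, falling to about 182 at an assumed 5% unconfirmed and 154 at 20%, assuming equal mortality and no interim correction.

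**What to change.** - Remove the not-confirmed exclusion from Box 1 and from the Exclusion criteria text.
- Define the primary analysis set as all enrolled patients with ED-suspected infection planned for hospitalization, whatever the later adjudication.
- Keep the adjudication, and report the confirmed-infection set as a sensitivity analysis.
- Report the number of unconfirmed patients and their outcomes.
- Align the population wording in the last paragraph of the Introduction with the aim, and give one time of confirmation in Diagnosis of infection, Box 1, Exclusion criteria and the Discussion.

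The cost is mainly an amendment to protocol and analysis wording, because these patients are already enrolled, scored and followed before the rule is applied. No extra inflation of the sample size is then needed for unconfirmed patients. The cohort becomes somewhat more heterogeneous, and performance estimates may move in either direction.

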### PASSEM study versus original derivation cohorts

The key characteristics of PASSEM Study and the original derivation cohorts of qSOFA, SIRS, and EWSs that will be assessed are shown in Table 4.

**Table 4 pone.0281208.t004:** Characteristics of PASSEM study and the original development cohorts of qSOFA score, SIRS criteria, NEWS/NEWS2, and MEWS.

Characteristic	PASSEM (n = 2,851)	qSOFA (n = 1,309,025)	SIRS (n = 519)	NEWS/NEWS2 (n = 35,585)	MEWS (n = 709)
**Data collection period**	2021–2022	2010–2012	1992	2006–2008	2000
**Study design**	Prospective cohort	Retrospective cohort	Prospective cohort	Retrospective cohort	Prospective cohort
**Setting**	30 EDs across 7 countries	12 community and academic hospitals in southwestern Pennsylvania (ED, hospital ward, and ICU)	42 ICUs in 40 US hospitals	MAU at Portsmouth hospitals NHS Trust, UK	MAU at District General Hospital (DGH), UK
**Definition of infection**	Based on opinion of attending ED physician	Combination of body fluid culture and nonprophylactic antibiotic administration in the EHR	NA	NA	NA
**Inclusion criteria**	Adult patients (age ≥18 yrs.) with suspected infection who presented to the ED and planned for hospitalization	Adult patients (age ≥18 yrs.) with suspected infection	Patients with sepsis who lack a clear source of infection	All general medical emergency patients aged ≥16 yrs., except for those transferred directly to critical care areas of the hospital	All medical emergency admissions admitted to the MAU
**Primary outcome**	30-days in-hospital mortality	In-hospital mortality	24-hours in-hospital mortality	24-hours in-hospital mortality	HDU or ICU admission, attendance of the cardiac arrest team at a cardiorespiratory emergency and death at 60 days
**Time window for measuring variables**	Initial presentation (at triage)	From 48 hrs. before to 24 hrs. after the onset of infection	Upon admission to ICU	NA	Twice daily for up to 5 days

***ED*:** Emergency department; ***EHR*:** Electronic health record; ***HDU*:** High dependency unit; ***ICU*:** Intensive care unit; ***MAU*:** Medical admission unit; ***NA*:** Not available; ***NHS*:** National Health Services; ***UK*:** United Kingdom; ***US*:** United States.

### Study flow chart

The study’s procedures and assessments are shown in Table 5. Patients will undergo 4 phases: screening (Time_-1_ [T_-1_], 1–2 days), enrolment (T_0_), and in-hospital (T_1_, maximum 30 days after T_0_), and out-hospital follow-up (T_2_, maximum 90 days after T_0_).

**Table 5 pone.0281208.t005:** Study’s procedures and assessments.

Study components	Phases			
	Screening	Enrolment	In hospital F/U	Out hospital F/U
**Eligibility screening**	X			
**Data collection**				
Demographics, medical history		X		
Physical examination/vital signs		X		
Blood investigations (WBCs count)		X		
**Primary outcome evaluation**				
In-hospital mortality (within 30 days)			X	
**Secondary outcomes evaluation**				
1. ICU admission			X	
2. ICU length of stay			X	
3. All-cause mortality (within 30 days)				X
4. All-cause mortality (within 90 days)				X

***F/U*:** Follow-up; ***WBCs*:** White blood cells

#### Screening and enrolment phases

A staff member will screen patients for eligibility and check their measured vital signs once they arrive at the ED (triage) and the investigator will enroll potentially eligible patients (i.e., age ≥18 years, with suspected infection, and planned for hospitalization). First, a web-based electronic data capture system (EDC) will assign each patient to a participant number in ascending order. Then, the investigator will collect and enter the patient’s initial data (demographics, contact information, Charlson Comorbidity Index (CCI) components, and variables required for qSOFA, SIRS, and EWS scores calculation) in an electronic case report form (eCRF) (see online supplementary materials). If the patient is not eligible, we will close the patient record in the EDC and clarify the cause of exclusion.

#### In-hospital follow-up

Once enrolment is completed, the in-hospital follow-up phase will start (T_1_, maximum 30 days after T_0_) (Table 5). Study team will monitor hospitalized patients’ status (i.e., death, alive and either discharged, transferred to another hospital, or still hospitalized) by consulting their specific medical registration number (MRN) in the recruiting center.

